## Abstract

**Background:** Group antenatal care has demonstrated promise as a service delivery model that may result in improved outcomes compared to standard antenatal care in socio-demographic populations at disparately high risk for poor perinatal outcomes. Intrigued by results from the United States showing lower preterm birth rates among high-risk women who participate in group antenatal care, partners working together as the Preterm Birth Initiative - Rwanda designed a trial to assess the impact of group antenatal care on gestational age at birth.

**Methods:** This study is a pair-matched cluster randomized controlled trial with four arms. Pairs randomized to group or standard care were further matched with other pairs into quadruples, within which one pair was assigned to implement basic obstetric ultrasound at the health center and early pregnancy testing at the community. At facilities randomized to group care, this will follow the opt-out model of service delivery and individual visits will always be available for those who need or prefer them. The primary outcome of interest is mean gestational age at birth among women who presented for antenatal care before 24 completed weeks of pregnancy and attended more than one antenatal care visit. Secondary outcomes of interest include attendance at antenatal and postnatal care, preterm birth rates, satisfaction of mothers and providers, and feasibility. A convenience sample of women will be recruited to participate in a longitudinal survey in which they will report such indicators as self-reported health-related behaviors and depressive symptoms. Providers will be surveyed about satisfaction and stress.

**Discussion:** This is the largest cluster randomized controlled trial of group antenatal and postnatal care ever conducted, and the first in a low- or middle-income country to examine the effect of this model on gestational age at birth.

**Trial registration:** This study is registered on ClinicalTrials.gov as
NCT03154177 May 16, 2017.

## Abbreviations

ANC, antenatal care, CHW, community health worker; CONSORT, Consolidated Standards of Reporting Trials; CRCT, cluster randomized controlled trial; DSMB, Data Safety and Monitoring Board; EDD, estimated date of delivery; GA, gestational age; LMIC, low- and middle-income country; MOH, Ministry of Health (Rwanda); PNC, postnatal care; PTB, preterm birth; PTBi – Rwanda, Preterm Birth Initiative – Rwanda; RBC, Rwanda Biomedical Center; RCT, Randomized controlled trial; REDCap, Research Electronic Data Capture; SPIRIT, Standard Protocol Items: Recommendations for Intervention Trials; UCSF, University of California, San Francisco; UPT, Urine pregnancy test; UR, University of Rwanda; WHO, World Health Organization.

## Introduction

Group antenatal care has demonstrated promise as a service delivery model that may be superior to standard antenatal care in socio-demographic populations at disparately high risk for poor perinatal outcomes, with no report of harms. Well-designed randomized controlled trials (RCTs) demonstrating improved outcomes among women and newborns after participation in group antenatal care (ANC) compared to standard ANC have been conducted in the United States
^1–
6^ and Sweden
^7^, which are classified as ‘high-income economies’ and Iran
^8,
9^, which is classified as an ‘upper middle-income economy
^10^.’ Benefits reported in these trials, at statistical significance, include greater gestational age (GA) at birth, greater birth weight, lower incidence of sexually transmitted infections, healthier maternal weight trajectories, fewer depressive symptoms, and increased satisfaction with care.

Among low-income countries, several small studies have reported on group ANC feasibility, acceptability, and prospective cohort outcomes. Only one has reported results of a small individual RCT. A prospective cohort trial in Ghana reported significantly higher health literacy among women who participated in group ANC
^11^. A pilot study in Tanzania and Malawi reported feasibility and acceptability and a significant increase in attendance at five ANC visits among women randomized to group ANC
^12,
13^. A cluster RCT currently underway in Bangladesh will report on ANC and postanatal care (PNC) service coverage, skilled birth attendance, and institutional deliveries
^14^, and this group has already reported start-up and implementation costs of group ANC delivery in that context, including the average cost per participant
^15^.

Given these studies and ongoing RCTs, implementation and policy teams around the world would like to know if group ANC will deliver significantly improved outcomes among women living in low-income economies, which bear the highest burden of maternal and neonatal mortality. Furthermore, the World Health Organization (WHO) encourages the provision of group ANC “by qualified health professionals . . . in the context of rigorous research, depending on a woman’s preferences . . .”
^16^ This call for research underscores the timeliness of such studies.

The Preterm Birth Initiative (PTBi) – Rwanda, aims to explore both the outcomes and feasibility of a combined group ANC and group PNC model implemented in Rwanda. PTBi – Rwanda is a partnership between investigators at the University of Rwanda (UR) and University of California, San Francisco (UCSF) and national health system implementors at the Rwanda Biomedical Center (RBC) and Ministry of Health (MOH). PTBi - Rwanda’s primary aim is to reduce the burden of morbidity and mortality related to prematurity. Intrigued by results from the United States showing lower preterm birth (PTB) rates among high-risk women who participate in group ANC, these partners aim to test the hypothesis that Rwandan women receiving care at facilities that offer group ANC will have a greater GA at birth, on average, than women receiving care at facilities that offer standard ANC. In addition, partners felt an important benefit of the approach was the ability to improve adherence to recommended ANC and PNC schedules, and also considered that additional components might produce similar effects. Specifically, partners wanted to study the effects of introducing urine pregnancy testing by community health workers as part of pregnancy surveillance and the use of ultrasound at first trimester to determine GA and motivate mothers to attend ANC earlier and more often.

Rwanda’s national maternity care system provides an excellent opportunity to test this innovative service delivery model due to its well-developed community capacity, cultural foundations in community-based decision-making and cooperation, and robust existing data system such as longitudinal ANC registers. The Rwanda MOH currently recommends four focused ANC visits and four PNC visits at 24 hours, 2 days, 3-7 days, and 42 days of life. The Rwanda Demographic and Health Survey published in 2015 provided a snapshot of the contemporary utilization of perinatal services
^17^. In Rwanda, 99% of pregnant women have attended at least one ANC visit with skilled medical personnel, while only 44% have attended the recommended four routine ANC visits. Of all births, 91% occur in a health care facility. While GA estimates are problematic as early ultrasound is not routinely available, 56% of women are reported to enter ANC before 16 weeks of pregnancy. About 19% of newborns receive a PNC assessment in the first two days after birth, but the proportion of women and newborns who receive PNC at about 42 days after birth has not yet been reported.

This article describes the design and intended evaluation of PTBi - Rwanda’s cluster RCT (CRCT) of a combined group ANC/PNC model, including primary and secondary outcomes, study population and sites, data collection methods, and data analysis plans.

## Methods

### Study aims

The primary aim of this study is to evaluate the effect of group antenatal care on gestational age at birth, at a cluster level. The secondary aims of this study are to determine the effects of: group antenatal care, screening obstetric ultrasound, and urine pregnancy testing in the community on antenatal care attendance and women’s and providers’ experience of antenatal and postnatal care; group antenatal care on preterm birth rates; group antenatal care on mode of birth; and group antenatal care on the outcomes of neonates at 42 days after birth, specifically among preterm neonates.

### Study design

The study is a pair-matched CRCT with four arms. In the five Rwandan districts selected for this study, we assessed 55 health centers to inform study design and site selection. First, we limited the data set to only those with an average of at least 48 first ANC per month, operating on the assumption that this would allow for formation of at least 2-4 ANC groups in the event the health center was allocated to the intervention. This gave us 50 potential health centers. We then limited to those that had more than one ANC provider during ANC days, which reduced the available health centers to 37. In total, 36 health centers (one was not matched to ensure pairing) were selected to participate in the study (see
*Extended data*: File 15)
^18^.

Next data on all other criteria for each health center was used to perform nonbipartite pair matching in R producing a list of strongest potential matches across all criteria. The study team then reviewed the possible matches and agreed on optimal pairings among facilities that had at least 2 ANC providers prioritizing matches with similar volume of ANC1 visits, and similar distance to the nearest district hospital. Within each pair, one facility was randomized to group ANC and PNC using a computer-generated random assignment and the other was randomized to continue delivering the standard models of focused ANC and PNC. Selected health centers were pair-matched based on 1) number of ANC providers, 2) ANC volume 3) delivery volume, 4) proportion of ANC1 before 16 weeks gestation, 5) baseline PTB rate, and 6) availability of key screening tests. Pairs were then further matched into quadruples by the study team based on ANC volume, where one pair within each quadruple was randomly assigned using a computer-generated random assignment to additionally implement basic obstetric ultrasound at the health center and early pregnancy testing at the community level and the other was not. No allocation concealment was used.

Therefore, each study facility has one of the four assignments as illustrated in
Figure 1. Arm 1 delivers standard ANC/PNC care only and is the pure control. Arm 2 delivers standard ANC and PNC care, with the addition of early pregnancy testing in the community and obstetric ultrasound performed by primary ANC providers. Arm 3 delivers group ANC/PNC, and Arm 4 delivers group ANC/PNC with the addition of early pregnancy testing and ultrasound. In health centers randomized to group care (Arms 3 and 4), this model will follow the opt-out standard of care for facility-based ANC and PNC. This design makes it possible to analyze differences between group care and standard care and also to assess if those effects are mediated by early pregnancy testing in the community or the availability of ultrasound (especially for early GA assessment) at the health center.

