### Sample size

Based on a review of RCT results included in the 2015 Cochrane Review of group versus conventional antenatal care for women
^24^, we assume the intraclass correlation coefficient (ICC) between Arms 1 and 2 and Arms 3 and 4 will be no larger than 0.01. We assume the standard deviation of GA at delivery is no larger than 4.3 weeks under both intervention and control arms. At 5% significance, with 36 facilities, this trial is powered (80%) to detect a 0.5-week difference in GA at delivery with 214 observations (ANC and outcome) per facility. Assuming a follow-up rate of 70%, 306 women per facility will be required. Just over 11,000 women will be recruited and we expect to follow almost 8,000 mother-newborn dyads through the period of the six-week PNC visit. At an average rate of 23 eligible recruits per month per facility, the total study duration will be (a) 14 recruitment months (from the end of May 2017 to August 2018, (b) an additional six to seven months to observe the outcomes of the last cohort of women recruited (February 2019), and (c) three additional months to complete data processing and analysis (May 2019).

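### Facility baseline preterm birth rate and early-attendance share were matched on before randomisation, but no outcome model commits to adjusting for them

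*Protocol article*

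**What the plan says.** **Baseline data and matching (Methods, Study design).** Six facility characteristics were used to form pairs, including "4) proportion of ANC1 before 16 weeks gestation, 5) baseline PTB rate, and 6) availability of key screening tests". The values were therefore held for all 36 facilities before allocation. An algorithm ranked possible matches on all criteria. The team then settled the pairs, "prioritizing matches with similar volume of ANC1 visits, and similar distance to the nearest district hospital". Group care was allocated inside pairs: "Within each pair, one facility was randomized to group ANC and PNC using a computer-generated random assignment". For the ultrasound and pregnancy-testing package, "Pairs were then further matched into quadruples by the study team based on ANC volume", and one pair in each quadruple was allocated to the package.

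**Models (Methods, Statistical analyses).** Model 1 is an unadjusted GEE. Model 2 adds only an adjustment for design effect, without naming pairs, quadruples or matching variables. Model 3 adds covariates that differ significantly and importantly between study groups, followed by backward Wald elimination at 0.05. A TMLE comparison would choose covariates by algorithm. Multi-level adjustment for facility characteristics is mentioned only as something to be considered.

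**Outcomes.** The primary outcome is mean gestational age (GA) at birth. Preterm birth and early ANC1 are secondary. Early ANC1 is before 14 weeks in Table 2 and before 16 weeks in Table 3.

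**Sample size.** "At 5% significance, with 36 facilities, this trial is powered (80%) to detect a 0.5-week difference in GA at delivery with 214 observations" per facility.

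**The concern.** In a trial of 36 clusters, facility-to-facility variation is a large part of the error. A pre-randomisation facility value of the outcome, or of something close to it, is an obvious covariate to fix in advance. It can remove part of that variation and correct chance imbalance, and it costs one degree of freedom.

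The article does not leave the covariate choice open. It states a rule, and the rule works against these variables. Entry to Model 3 depends on an observed difference between study groups. Matching on a variable makes such a difference less likely, however strongly the variable predicts outcome. A covariate chosen from the data also gives an adjusted estimate whose form is not known until the data are seen.

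The package contrast is the most exposed. Its quadruples were formed on ANC volume, so baseline early attendance was not a stated criterion when 9 of the 18 pairs were allocated to the package. Yet earlier attendance is the stated goal of community testing, and the effect of the package on attendance is a secondary aim.

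**Working it through.** **1. Inputs from Sample size.** Difference 0.5 weeks; "standard deviation of GA at delivery is no larger than 4.3 weeks"; ICC "will be no larger than 0.01"; 36 facilities, so 18 v 18; 5% significance (taken as two-sided); 80% power. Also: "Assuming a follow-up rate of 70%, 306 women per facility will be required".

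**2. The plan's own figure.**
- Per arm without clustering: n = 2 × 4.3² × (1.960 + 0.842)² / 0.5² = 1161.0.
- Cluster size with one facility per arm held back: m = n(1 − ICC) / (17 − n × ICC) = 1161.0 × 0.99 / (17 − 11.61) = 213.2, so 214.
- A noncentral t calculation on 36 facility means (34 df) also gives 214 and 80.0%.
- 214 / 0.70 = 305.7, so 306.

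The stated figures reproduce with no credit for matching or baseline adjustment.

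**3. Between-facility share of the variance of a facility mean.** Share = ICC × m / [1 + (m − 1) × ICC].
- ICC 0.01: 2.14 / 3.13 = 68%
- ICC 0.005: 1.07 / 2.065 = 52%
- ICC 0.001: 0.214 / 1.213 = 18%

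The plan's ICC is an upper bound, so 68% is a ceiling.

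**4. Possible gain for GA, pairs ignored.** Let R² be the proportion of between-facility variance that the baseline explains. It is not in the documents; 0 to 0.50 is assumed. SE ratio = √(1 − share × R²). At ICC 0.01 the unadjusted SE is 0.173.

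| R² | SE ratio | Power for 0.5 weeks (33 df) |
|---|---|---|
| 0 | 1.000 | 79.9% |
| 0.10 | 0.965 | 82.7% |
| 0.25 | 0.911 | 86.8% |
| 0.50 | 0.811 | 93.2% |

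The R² = 0 row is the cost of a useless covariate: 80.0% falls to 79.9%. At R² = 0.25 the SE ratio is 0.933 for ICC 0.005 and 0.978 for ICC 0.001.

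**5. Possible gain with pairs kept, ICC 0.01.** A paired analysis has 17 df, or 16 with one covariate.
- Pairs already explain 25% of between-facility variance (assumed): power 84.7%. Explaining a further 10% of the remainder gives 86.6%.
- Pairs already explain 50% (assumed): 91.8% becomes 92.9%.
- A useless covariate costs 0.2 to 0.3 points in these two cases.

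**6. Package contrast, early attendance.** The Introduction gives 56% entering before 16 weeks. The ICC is not in the documents; 0.01 to 0.10 is assumed. Between-facility SD = √(ICC × 0.56 × 0.44). With 9 v 9 pairs and within-pair correlation ρ in the baseline, the SD of the chance difference between package and non-package facilities is that SD × √[(1 + ρ) / 9].

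| ICC | ρ = 0 | ρ = 0.5 | ρ = 0.8 |
|---|---|---|---|
| 0.01 | 1.7 points | 2.0 | 2.2 |
| 0.05 | 3.7 | 4.5 | 5.0 |
| 0.10 | 5.2 | 6.4 | 7.0 |

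Pairing on early attendance raises ρ, so it helps the group-care contrast but makes the package contrast more variable. The table gives no credit for any correlation between ANC volume and early attendance.

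**7. Cost for the package contrast.** Nine quadruples leave about 8 df. One covariate raises the critical t from 2.31 (8 df) to 2.36 (7 df). On that count alone, the covariate must explain about 1 − (2.306 / 2.365)² = 5% of the residual variance to break even.

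**The case against.** **Covariates belong in the analysis plan, which is not shown.** That would answer a mere gap. Here the article states the selection rule, so the point concerns a stated method. A separate plan may still fix it better.

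**The baselines were used in the design.** This stands in large part. Both were matching criteria, which limits imbalance for the primary contrast of group with standard care. What remains is the within-pair difference, which may be real because the final pairings gave priority to volume and distance. No model names the pairs, so the text does not commit to recovering what matching could give.

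**The models could include these variables.** True. Model 3's Wald step keeps covariates by association with outcome, and the TMLE and multi-level options could use facility values. None commits to them, and the between-group test may stop them before the Wald step.

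**The PTB rate is not a baseline of the primary outcome.** This stands. No baseline mean GA is described, so the PTB rate is a proxy for GA, although it is a direct baseline for preterm birth. The Introduction itself calls GA estimates problematic for want of early ultrasound, which argues for the lower end of the R² range. The 16-week share matches the Table 3 outcome exactly and the 14-week outcome in Table 2 only approximately.

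**A stronger reading.** A reader might infer that precision is certainly being thrown away, or that the trial is underpowered. The documents support neither. They give no baseline-outcome correlation, and 214, 306 and 80% all reproduce without adjustment.

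**Conclusion.** The concern holds in a limited form. Two relevant facility baselines were available before randomisation, and no stated outcome model commits to them. The one explicit covariate rule tends to exclude them because they were matched on. Precision may be lost and residual chance imbalance may remain.

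For GA, the power gain would be about 3 to 13 points if the baseline explains 10% to 50% of between-facility variance, the ICC is at its ceiling of 0.01 and the pairs are ignored. With pairs kept, a further 10% explained is worth about 1 to 2 points. The reduction in SE is smaller at a lower ICC. Every gain rests on an assumed R².

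The case is strongest for early attendance under the package contrast. There, matching does not protect the baseline, and the chance imbalance could have an SD of about 2 to 7 points across the assumed ICCs and correlations. This is a recommended improvement, not an error in a stated figure.

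**What to change.** Before arm-level results are seen, specify the following, regardless of any significance test and alongside the pair or quadruple structure:

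- Adjusted models for GA at birth and preterm birth include the facility's baseline PTB rate.
- Adjusted models for early ANC1, above all the package contrast, include the facility's baseline share of ANC1 before 16 weeks. State whether the outcome uses the 14-week or the 16-week cut-off, since Tables 2 and 3 differ.
- The estimate without baseline adjustment is reported as supportive.

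The Study status section says that enrolment and data collection have ended and analysis is under way, so timing matters. If arm comparisons have already been seen, the report should say so.

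The cost is one line of text and one degree of freedom per model, with no new data. If the covariate proves useless, the primary contrast loses about 0.1 power point with pairs ignored, or 0.2 to 0.3 with pairs kept. The package contrast loses somewhat more, because only about 8 df are available.

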**Figure 1. f1:**
[figure not shown]
Facility-level randomization of 36 health centers included in a cluster randomized controlled trial of group antenatal care and postnatal care in Rwanda. Arm 1 delivers standard antenatal and postnatal care only and is the pure control. Arm 2 delivers standard antenatal and postnatal care, with the addition of early pregnancy testing in the community and obstetric ultrasound performed by primary antenatal care providers. Arm 3 delivers group antenatal and postnatal care, and Arm 4 delivers group antenatal and postnatal care with the addition of early pregnancy testing and ultrasound. In health centers randomized to group care (Arms 3 and 4), this model will follow the opt-out standard of care for facility-based antenatal and postnatal care. This design makes it possible to analyze differences between group care and standard care and also to assess if those effects are mediated by early pregnancy testing in the community or the availability of ultrasound (especially for early gestational age assessment) at the health center. HC, health center; US, ultrasound; PT, pregnancy testing.

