Those providers and CHWs associated with sites randomized to group ANC were invited to a three-day training workshop on a rotating basis to minimize the impact on service provision. This workshop brought providers and CHWs together in joint training activities for the first time ever. Training occurred in large- and small-group circles to replicate as closely as possible the principles of successful group care. Activities focused on principles of adult learning, facilitation skills, a review of the Rwanda ANC/PNC packages of care, health assessment skills, how to organize and facilitate a group visit, and role-play practice of each of the group ANC/PNC curriculum discussion topics with feedback and re-practice.

These new group ANC facilitators were trained in all aspects of model fidelity by a team of six Rwandan group ANC Master Trainers
^22^. The Master Trainers, five midwives and one physician, who all have separate employment, were recruited based on their excellent facilitation skills, expertise in maternal and newborn health, and commitment to the project. The Master Trainers will make scheduled visits to each health center providing group ANC, with decreasing frequency over time, and unscheduled visits will be made as needed. During these visits, Master Trainers will observe group ANC as it is delivered and collect data about model fidelity. They will also offer supportive feedback and will model for group ANC facilitators how to plan for and debrief after each visit.

Study sites assigned to either Arm 2 or Arm 4 are randomized to introduce basic obstetric ultrasound by ANC providers at the health center and urine pregnancy testing by CHWs in the community (
Figure 1). The objective of screening ultrasound at the health center level is to more accurately assign the EDD, but providers are also trained to screen for gross abnormalities. The goal of community-based pregnancy testing is to engage women in earlier ANC attendance, which in turn may identify and promote early referral of at-risk pregnancies for physician consultation at district hospitals.

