### Statistical analyses

To compare the study groups, socio-demographic and reproductive health characteristics, and health care facility descriptive bivariate analyses stratified by study arm will be conducted using Chi-square and Student’s t-test statistics for categorical and continuous data, respectively. Similar unadjusted bivariate analyses will be presented for the primary and secondary outcomes. Unadjusted, intention-to-treat generalized estimating equations (GEE) linear regression with robust variance estimation analyses will be conducted to assess the effectiveness of the treatment regimen on the primary outcome variable, gestation at delivery, and analogous linear and logistic analyses of will be conducted to assess continuous and categorical secondary outcomes (Model 1). For these outcomes, similar analyses will be conducted to control for design effect (Model 2) and the effects of any additional unforeseen differences in measured study group characteristics (Model 3). Model 3 will include all covariates that are statistically significant and judged as important differences between the study group (e.g. not simply significantly different due to large sample size) as identified by a backward stepwise Wald analysis (Model 3), which removes the covariate least associated with the outcome, and continues in that manner to remove covariates not significantly associated with the outcome at the α=0.05 level.

Model 1: Outcome=Independent Causal VariableModel 2: Outcome=Independent Causal Variable, adjusted for design effectModel 3: Outcome=Independent Causal Variable, adjusted for design effect plus (retained) covariates

Additionally, we propose comparing these methods with data-adaptive targeted maximum likelihood estimators (TMLE)
^25^. These would attempt to leverage the hierarchical structure of the data and would adjust for covariates through a data-adaptive algorithm. Multi-level analyses to adjust for facility-level characteristics will be considered.

The main analyses will compare the control group (Arms 1+2) with the intervention group (Arms 3+4). Subanalyses by study arm will be conducted.

Arm 1: Standard ANC/PNC careArm 2: Standard ANC/PNC care, with early pregnancy testing and ultrasoundArm 3: Group ANC/PNC onlyArm 4: Group ANC/PNC care, with early pregnancy testing and ultrasound

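### The ultrasound and pregnancy-testing package was randomised to pairs of health centers, so a pooled test of the package needs the pair as its unit and the quadruple as its stratum, which the plan does not say

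*Protocol article*

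**What the plan says.** The Study design section describes two randomisations with two different units.

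- Group care: "Within each pair, one facility was randomized to group ANC and PNC using a computer-generated random assignment". The unit is the facility, within a pair.
- Package: "Pairs were then further matched into quadruples by the study team based on ANC volume", and then "one pair within each quadruple was randomly assigned using a computer-generated random assignment to additionally implement basic obstetric ultrasound". The unit is the pair, within a quadruple.

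Two other places are looser. The Figure 1 legend labels the whole four-arm allocation "Facility-level randomization of 36 health centers included in a cluster randomized controlled trial". Study interventions says "Study sites assigned to either Arm 2 or Arm 4 are randomized to introduce basic obstetric ultrasound".

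Study aims makes the effect of "screening obstetric ultrasound, and urine pregnancy testing in the community on antenatal care attendance" a secondary aim. Outcomes and processes for comparison promises to report the effects of both package components, and the Discussion expects insight into early uptake and visit adherence.

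Statistical analyses sets the main contrast as Arms 1+2 against Arms 3+4 and adds "Subanalyses by study arm will be conducted". It uses one GEE family with robust variance for all outcomes, with Model 2 adjusted for an unspecified design effect. It names no clustering unit and no pair or quadruple term. TMLE using the hierarchical structure is proposed, and multi-level analyses are to be considered.

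**The concern.** Both facilities of a pair always carry the same package assignment. If the package's main effect is tested by pooling Arms 2+4 against Arms 1+3 with facilities as independent units, 36 units are counted where 18 were randomised.

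The direction differs from the familiar case of ignoring pairs in the group-care contrast. There the pair effect cancels from the true variance, and ignoring pairing is conservative. Here the pair effect adds to the true variance, and ignoring it can make standard errors too small. Pair fixed effects cannot repair this, because the package is constant within a pair and would drop out of the model.

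At stake are the standard errors, intervals and p-values for the package effect on early attendance, four-visit attendance and the other secondary outcomes. The matching gives some reason to expect the anti-conservative direction. Pairs were matched on six criteria, including the proportion of first visits before 16 weeks, the cut-off that Table 3 uses for early attendance. Quadruples were matched on ANC volume only.

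**Working it through.** **Units.** "In total, 36 health centers (one was not matched to ensure pairing) were selected to participate in the study". 36 facilities = 18 pairs = 9 quadruples, so the package compares 9 pairs with 9 pairs.

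**The plan's own figure (Sample size section; sized for group care, not the package).** Design effect 1 + 213 × 0.01 = 3.13. Effective number per arm 18 × 214 / 3.13 = 1,230.7. SE = 4.3 × √(2/1,230.7) = 0.173 weeks, and 0.5/0.173 = 2.88. A two-sided t-test on 34 df then has 80.0% power, and 214 is the smallest number per facility that reaches 80%. Also 214/0.70 = 306. The figure reproduces with the facility as unit, which is right for group care. No power or error rate is stated for the package.

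**Variances.** Let q, p and f be the quadruple, pair and facility variances of a facility mean, with f including sampling error.

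- Pooled package contrast: quadruple effects cancel. True variance (2p + f)/9; facility-level estimate about (q + p + f)/9. Too small if p > q, too large if q > p.
- Group-care contrast: true variance f/9; facility-level estimate about (q + p + f)/9. Never too small.
- Arm 2 v 1, or Arm 4 v 3: each uses one facility from any pair. True variance 2(p + f)/9; facility-level estimate 2(q + p + f)/9. Correct or conservative.

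**One case by hand.** Put total variance at 1, ICC 0.01, 214 women per facility. Sampling error is 0.99/214 = 0.00463. If pairs share half the between-facility variance and quadruples none, p = 0.005, q = 0 and f = 0.005 + 0.00463 = 0.00963. The ratio of true to estimated variance is (0.010 + 0.00963)/(0.005 + 0.00963) = 1.34. A nominal 1.96 limit becomes 1.96/√1.34 = 1.69, a two-sided rate of about 9%.

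**Simulated false-positive rates for the pooled contrast**, nominal 5%, ICC 0.01, 214 women per facility, 60,000 null trials per row. The shares of between-facility variance are assumptions.

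| Pair share | Quadruple share | Facility t (34 df) | Quadruple-difference t (8 df) |
|---|---|---|---|
| 0 | 0 | 5.0% | 5.2% |
| 25% | 0 | 7.2% | 5.1% |
| 50% | 0 | 9.2% | 5.2% |
| 75% | 0 | 11.5% | 5.0% |
| 100% | 0 | 14.0% | 4.9% |
| 25% | 25% | 5.2% | 4.9% |
| 50% | 25% | 7.4% | 5.1% |
| 50% | 50% | 6.1% | 5.1% |
| 25% | 50% | 3.9% | 5.2% |
| 0 | 50% | 2.0% | 5.0% |

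The ICC of 0.01 is the plan's value for gestational age; none is given for attendance. At ICC 0.05 to 0.10 the facility t-test runs from about 1% to 18% over the same shares, and the 8-df test stays near 5%.

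**Single-arm check.** At ICC 0.05, pair share 50% and quadruple share 0, a facility t-test of Arm 2 v 1 rejects 5.1%, against 11.0% for the pooled contrast. With a quadruple share of 20% the Arm 2 v 1 test rejects 3.1%.

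**The case against.** The strongest reply is that the document never specifies the faulty test. Study design states the pair-level assignment correctly, and the legend and the Study interventions sentence only say which sites carry the package. Statistical analyses does not name the pooled contrast or a clustering unit. The subanalyses by arm that it does name lack the anti-conservative error if they are comparisons such as Arm 2 v 1. The clustering level of a secondary analysis may also stand in an SAP that is not shown.

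Most of this stands. A reader might infer that the plan commits to a facility-level test of the package with a false-positive rate of 11 to 13%. The documents do not support that:

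- The health-center aggregation in Table 2 applies only to gestational age; attendance outcomes are compared across arms. The 36 facilities in Sample size serve the group-care contrast.
- A rate of 11 to 13% needs a correlation of about 0.5 to 0.6 between the facility means of a pair and none within quadruples. Neither is given. Quadruples were deliberately matched, and ANC volume was a priority in the pairing too, which weakens the case that p exceeds q.
- Rates from an uncorrected robust z-test overstate the unit error. With no pair or quadruple correlation that test already rejects 6.6%, from small-sample bias alone.

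What remains is that the document describes the randomised unit in two ways, promises a package effect, and gives one model family that does not separate the two factors. Pooling Arms 2+4 against Arms 1+3 is the natural way to estimate that effect.

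**Conclusion.** The point holds conditionally. The package was randomised to 18 pairs in 9 quadruples, and two places describe this loosely. If its main effect is tested by pooling Arms 2+4 v 1+3 with facilities as independent units, the error rate is wrong by an amount the document does not allow one to fix.

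At the plan's ICC the range is about 2% to 14%: 7.2% to 11.5% if pairs share 25% to 75% of the between-facility variance and quadruples none, 5.2% to 6.1% if the shares are equal, and below 5% if quadruples share more. These figures rest on assumed shares, normally distributed effects, equal facility sizes and an ICC stated for gestational age.

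The primary analysis is unaffected by this anti-conservative error. The case for changing the wording does not depend on the assumed shares, because the pair-within-quadruple test held 4.8% to 5.2% in every scenario, including those at ICC 0.05 and 0.10.

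**What to change.** - In the Figure 1 legend and Study interventions, say that the package was randomised to pairs within quadruples, as Study design does.
- In Statistical analyses, say that any pooled package effect takes the pair as unit and the quadruple as stratum. Options are a t-test on the nine within-quadruple differences in pair means (8 df), a permutation test over the 2^9 = 512 allocations, or a mixed model with quadruple, pair and facility levels that tests the package against the pair stratum.
- Keep the group-care contrast and the group-care-by-package interaction in the within-pair stratum.

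This needs no new data or participants. The price is 8 rather than 34 degrees of freedom and usually wider intervals for a secondary aim. Study status reports that analysis is under way, so the wording should be settled before package results are reported.
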